#### Secondary outcomes

Catheter longevity, the rate of surgical complications, mortality, leakage, catheter migration, re-admissions, infections, and duration of hospital stay. The quality of life and pain score. The use of postoperative pain medication. Percentage of functioning PD catheters at 6 months postoperatively.

### Treatment of participating PD patients

All patients will be treated according to the intention to treat principle. Treatment and outpatient clinic visits will be in accordance with the current standard protocol. Patients will be asked to fill out different standardised questionnaires to evaluate pain and nausea (VAS-score), and quality of life (SF-36 and EQ-5D). (Table 1)

### Statistical analysis

#### Descriptive statistics

Categorical variables will be presented as numbers (percentages). Continuous variables will be presented as medians (ranges). Categorical variables will be compared with the Chi-square test. Continuous variables will be compared with the Mann-Whitney-U test. All analyses will be conducted using SPSS (version 17.0, SPSS Inc., Chicago, USA). A P-value <0.05 (two-sided) will be considered statistically significant.

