### Study design

The LOCI-trial is a multicenter prospective single blinded, randomized controlled trial. The LOCI-trial has a pilot nature, as the study will generate data that should enable us to design a large multi-center randomised controlled trial comparing the laparoscopic PD insertion technique with the open technique.

The design of this protocol is in accordance with the CONSORT guideline [20]. We have stratified per center, PD in the past and previous episodes of peritonitis. The study has started on May 24^th ^2011 and the duration will be approximately 1.5 years. This study compares laparoscopic and open PD catheter insertion. In total 100 patients will be included in the study. Approval of the Medical Ethical Committee Erasmus MC, Rotterdam, The Netherlands, was obtained.

Randomisation will take place after endotracheal intubation, by means of a web-based computer programme with supervision of the study coordinator. This computer programme will generate the randomisation sequence. The patient will be blinded for the operation technique in the postoperative period. The wounds will be covered with a standard pattern of bandages [21]. All patients will fill out questionnaires (the Short-Form 36 (SF-36), EuroQol (EQ-5D) and a Visual Analogue Scale (VAS) for pain) until 6 months postoperatively. (Table 1)

**Table 1 T1:** Time schedule for filling out the questionnaires

Time of evaluation	VAS	EuroQol	SF-36
Preoperative	X	X	X
Postoperative			
Day 0	X		
Day 1	X		
Day 2	X		
Day 3	X	X	
Week 1	X	X	
Week 2	X	X	
Week 4		X	X
Week 6			X
Week 8			X
Week 12		X	X
Week 26		X	X

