### Sample size calculation

At present, we do not have sufficient data to perform a power analysis. Therefore, this pilot study will include two groups of 50 patients. We anticipate that these 100 patients will be sufficient to indicate a difference in technical failure rate at 6 weeks. We do not expect to find significant differences in secondary end points in this relatively small number of patients. In order to be able to include the number of required patients, this study will take place in multiple hospitals. Based on the outcome of this pilot study, we will design a larger multicenter randomized controlled trial, including a large number of patients based on a power calculation.

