### Outcome measures

#### Primary outcome

The percentage of functioning CAPD catheters at 6 weeks postoperatively. This is defined by not having an indication for catheter removal or revision for:

• An in- and/or outflow restriction. Outflow restriction is defined as an outflow time longer than 30 minutes, and urokinase treatment has failed.

• Refractory peritonitis, relapse peritonitis or fungal peritonitis, as described in the national guidelines defined by the Dutch Federation of Nephrology.

• Severe abdominal pain (VAS > 8) for 4 weeks.

• Pericanullar or subcutaneous leakage of peritoneal fluid not improving spontaneously within 5 weeks after catheter insertion.

• Tunnel- or exit-site infection not responding to treatment in 2 weeks (refractory infection).

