#### Univariate analysis

Categorical variables will be compared with the Chi-square test. Continuous variables will be compared with the Mann-Whitney-U test or the two sample unpaired t-test.

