#### Multivariate analysis

Logistic regression will be applied to determine the independent effects of age, gender, ASA classification, body mass index, reason ESRD, time of surgery, medical history, previous PD catheter insertion and previous abdominal surgery on catheter survival.

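### Randomisation is stratified on three factors but the stated test for the primary outcome uses none of them; the test stays valid, and loses efficiency only if the strata predict failure

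*Protocol article*

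**What the plan says.** Study design in the Protocol article fixes the randomisation: "We have stratified per center, PD in the past and previous episodes of peritonitis". The primary outcome is binary at patient level: "The percentage of functioning CAPD catheters at 6 weeks postoperatively".

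Descriptive statistics gives the comparison, "Categorical variables will be compared with the Chi-square test", and the criterion, "A P-value <0.05 (two-sided) will be considered statistically significant". Univariate analysis repeats the chi-square test and adds, for other variables, "Continuous variables will be compared with the Mann-Whitney-U test or the two sample unpaired t-test". None of these tests is stratified or adjusted. The article does not tie the chi-square test to the primary outcome by name, but it is the only named between-arm test that fits a binary outcome.

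Multivariate analysis describes a logistic regression whose list of factors ends "medical history, previous PD catheter insertion and previous abdominal surgery on catheter survival". The list contains neither treatment arm nor centre. Past PD is roughly covered by earlier catheter insertion. Earlier peritonitis is not named, though the unspecified medical history item could include it.

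On size, Sample size calculation says "Therefore, this pilot study will include two groups of 50 patients" and gives as the reason "At present, we do not have sufficient data to perform a power analysis".

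**The concern.** Stratified randomisation balances the arms within each stratum, so differences between strata contribute little to the chance variation of the treatment difference. Pearson's chi-square takes its variance from the pooled failure rate and still counts the between-stratum part as noise. If the strata predict failure, that variance is larger than the design produces. The P-value is then too large on average, and an unstratified confidence interval would be too wide.

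What is at stake is efficiency and agreement between design and analysis. The trial is small, and Sample size calculation nevertheless expects its 100 patients to indicate a difference at 6 weeks. It is also meant to inform a larger trial, so the way it handles the strata may be carried forward.

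**Working it through.** **Inputs from the article.** 50 per arm; two-sided 0.05; three stratification factors. The failure rates of 35% (open, an upper figure) and 13% (laparoscopic) are the literature values in the Abstract, not design assumptions.

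**Inputs assumed, because the article gives none of them.** Number of centres (3), permuted blocks of 4, how common past PD is, the share of those patients with earlier peritonitis (half), and how strongly each factor predicts failure.

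**Step 1: power of the plain test.** The article states no power, so there is no figure to reproduce. By the usual formula, with mean rate (0.35 + 0.13)/2 = 0.24:

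- standard error under no difference: √(2 × 0.24 × 0.76 / 50) = 0.0854
- standard error under 35% v 13%: √((0.35 × 0.65 + 0.13 × 0.87) / 50) = 0.0825
- z = (0.22 − 1.96 × 0.0854) / 0.0825 = 0.637, so power = 73.8%

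Power of 80% would need 58 per arm.

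**Step 2: why the test becomes conservative.** Under balanced stratified allocation and no treatment effect, the true variance of the difference divided by the variance the chi-square uses is about

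mean of p_s(1 − p_s) over strata ÷ p(1 − p), with p the overall rate.

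Take the strong scenario below at an overall rate of 24%. Stratum failure rates in the three centres are 0.075, 0.145, 0.261 (no past PD, weight 0.2333 each); 0.196, 0.337, 0.514 (past PD only, weight 0.05 each); and 0.327, 0.504, 0.679 (past PD and peritonitis, weight 0.05 each). The weighted mean of p_s(1 − p_s) is 0.0901 + 0.0315 + 0.0344 = 0.156. Then 0.156 / (0.24 × 0.76) = 0.855, and 1.96 / √0.855 = 2.12, a true two-sided error of about 3.4%. The simulation gives 3.6%.

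**Step 3: simulation.** 20,000 trials per setting, N = 100, blocks within centre × past PD × peritonitis; Pearson chi-square against Cochran-Mantel-Haenszel (CMH). Type I error is at 24% failure in both arms (35% in brackets); power is at 35% v 13%.

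| Strata (odds ratios for past PD and peritonitis; centre SD on the log-odds scale; share with past PD) | Chi-square type I | CMH type I | Chi-square power | CMH power |
|---|---|---|---|---|
| Not prognostic (1; 1; 0; 20%) | 5.2% (5.3%) | 5.0% (5.0%) | 74.8% | 73.6% |
| Moderate (2; 1.5; 0.3; 20%) | 4.9% (4.7%) | 5.1% (5.0%) | 75.3% | 75.0% |
| Strong (3; 2; 0.6; 30%) | 3.6% (3.5%) | 4.8% (4.8%) | 76.4% | 79.7% |
| Extreme (5; 3; 1.0; 40%) | 2.3% (2.3%) | 4.8% (5.0%) | 78.3% | 86.0% |

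The power of the plain test does not fall as the strata strengthen (74.8% to 78.3%). The loss is relative to a test that uses the strata: 79.7 − 76.4 = 3.3 points when strong and 86.0 − 78.3 = 7.7 when extreme.

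**Step 4: sensitivity to the number of centres.** A repeat with 4 centres widens the results to ranges. With null or moderate strata, chi-square error stays near 5% and CMH has up to about 3 points less power. With strong strata, error is about 3.5–3.7% and the loss 1–3 points. With extreme strata, about 2.3–3.0% and 6–8 points.

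**Step 5: sparseness.** With 3 centres, 20% past PD and half of those with peritonitis, each past-PD stratum expects 100 × 0.20 × 0.5 / 3 = 3.3 patients. A stratum whose patients are all in one arm adds nothing to CMH. This is where the small cost in the null setting comes from.

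**The case against.** The strongest reply is that nothing is wrong with the test as a test. In every setting with prognostic strata its error rate is at or below 5%, so false positives are not inflated. This stands, and it rules out one tempting inference: that ignoring the strata biases the comparison or leaves centre differences confounded with treatment. Stratified allocation has already balanced the arms.

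A second reply is that the loss is conditional. A reader might infer that the three factors were chosen because they predict failure, so that lost power is certain and perhaps ten points or more. The article gives no reason for choosing them and quotes no prognostic effect. With null or moderate strata there is no loss, and even the extreme setting costs about 8 points. There are hints of relevance: severe forms of peritonitis count towards the primary outcome, and earlier catheter insertion is listed as a candidate predictor. Hints do not fix a size.

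A third reply is that this is an unpowered pilot with many small strata, so a few points matter less and the stratified test has its own cost. Both stand in part. The pilot status lowers the stakes without removing the article's expectation of seeing a difference at 6 weeks. The sparseness means that a pooling rule is needed.

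Last, covariate detail may sit in a full protocol or analysis plan that is not shown. That is fair for the content of the medical history item. It does not undo the article's own choice of an unstratified test.

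**Conclusion.** The mismatch is on the page: three stratification factors in the randomisation, none in the stated test of the primary outcome, and a logistic model without treatment arm or centre. It is a point of efficiency and consistency, not of validity or bias.

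Its size runs from nothing (null or moderate strata), through 1–3 power points (strong), to 6–8 (extreme). These figures rest on 50 per arm, 35% v 13%, blocks of 4, three or four centres and assumed stratum effects. Confidence is high that design and analysis do not match, and only moderate on how much that costs. The change is worth making because the possible gain exceeds the possible loss and the work is small.

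**What to change.** Name one primary comparison at 6 weeks that uses the randomisation strata, and the same one at 6 months. There are two suitable forms:

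- a CMH test with the Mantel-Haenszel risk difference, Σ w_s d_s / Σ w_s with w_s = n_1s n_0s / n_s, and its 95% CI; or
- a logistic model with treatment arm plus centre, past PD and earlier peritonitis. At 35% v 13% only 50 × 0.35 + 50 × 0.13 = 24 failures are expected, so its terms must be few.

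Fix in advance how small centres and sparse strata are pooled, to be applied without sight of outcome by arm. Keep the plain chi-square as a sensitivity analysis, and describe the existing logistic regression as a risk-factor analysis.

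The cost is wording plus the pooling rule, since the strata are already recorded for randomisation. The statistical downside is about 1–3 power points if the strata turn out not to be prognostic.

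### For pain and quality of life the article names only unadjusted two-sample tests, although each scale is measured before surgery and repeatedly afterwards, and two sections differ on which test applies

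*Protocol article*

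**What the plan says.** The Statistical analysis section gives general rules by type of variable. Under Descriptive statistics, "Continuous variables will be compared with the Mann-Whitney-U test". Under Univariate analysis, "Continuous variables will be compared with the Mann-Whitney-U test or the two sample unpaired t-test". The significance rule is "A P-value <0.05 (two-sided) will be considered statistically significant", and no adjustment for multiple testing is mentioned.

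The only model with covariates is under Multivariate analysis: "Logistic regression will be applied to determine the independent effects of age, gender, ASA classification, body mass index, reason ESRD, time of surgery", followed by history items. Its outcome is catheter survival. It contains no pain or quality-of-life score and does not cover those outcomes.

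Table 1 of the protocol article ("Time schedule for filling out the questionnaires") marks all three instruments before surgery ("Preoperative X X X") and at several later times. The Secondary outcomes section lists "The quality of life and pain score" without a time point or summary measure. The abstract ties quality of life to 6 months. No section gives a time for pain.

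The Sample size calculation section states: "We do not expect to find significant differences in secondary end points in this relatively small number of patients".

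**The concern.** A baseline score is usually the strongest predictor of the same score later. Randomisation follows intubation (Study design), so the preoperative questionnaires precede allocation and are valid covariates. The trial asks patients for these data, but the named tests, applied to postoperative scores, would not use them. Nor do the tests combine a patient's successive scores. With 50 patients per group, lost precision matters, and more so because the pilot is meant to inform a larger trial.

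The two sections also differ. One fixes a rank test; the other allows a rank test or a t-test. With no rule, the choice could be made after the data are seen.

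Finally, a 5% threshold applied to several scales at several times would produce chance findings, if that is how the tests were used.

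**Working it through.** The article states no power, standard deviation, baseline correlation or number of tests for these outcomes, so it has no figure to reproduce. The group size is consistent: 2 × 50 = 100.

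**1. Postoperative times in Table 1**

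| Instrument | Postoperative times | Count |
|---|---|---|
| VAS | days 0, 1, 2, 3; weeks 1, 2 | 6 |
| EuroQol | day 3; weeks 1, 2, 4, 12, 26 | 6 |
| SF-36 | weeks 4, 6, 8, 12, 26 | 5 |

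Total: 6 + 6 + 5 = 17. This counts one score per instrument per time.

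**2. Gain from baseline adjustment**

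With correlation ρ between the preoperative and later score, a linear baseline-adjusted comparison has variance 1 − ρ² relative to an unadjusted comparison of means. A change score has 2(1 − ρ). The power columns use 50 per group, two-sided 5% and an assumed difference of 0.5 SD. Unadjusted power is 70.5%.

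| Assumed ρ | Adjusted variance, 1 − ρ² | Reduction | Change-score variance, 2(1 − ρ) | Power with adjustment |
|---|---|---|---|---|
| 0.3 | 0.91 | 9% | 1.40 | 74.6% |
| 0.5 | 0.75 | 25% | 1.00 | 82.3% |
| 0.7 | 0.51 | 49% | 0.60 | 93.8% |

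At ρ = 0.5, 1/0.75 = 1.33, so adjustment is worth about a third more patients. A change score has a larger variance than adjustment in all three rows. At ρ = 0.3 it is also worse than ignoring baseline.

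**3. False positives, if each scheduled time were tested once per instrument**

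Expected number when no true difference exists: 17 × 0.05 = 0.85, whatever the correlation.

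Chance of at least one, if the tests were independent: 1 − 0.95¹⁷ = 0.582, or 58%.

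Repeated scores on the same patients are correlated, so independence gives the upper end of the range considered. Simulation of 17 Mann-Whitney tests (50 per group, 4,000 runs, assumed correlation r within an instrument and r/2 between instruments) gave:

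| r | Chance of at least one P < 0.05 |
|---|---|
| 0 | 58% |
| 0.3 | 53% |
| 0.5 | 46% |
| 0.7 | 38% |
| 0.9 | 26% |

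The r = 0 row agrees with the formula. A Bonferroni threshold over 17 tests would be 0.05/17 = 0.0029.

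**4. The two statistical sections side by side**

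Descriptive statistics names the Mann-Whitney test alone. Univariate analysis names Mann-Whitney or the unpaired t-test. Neither links a test to a particular outcome or to a distributional condition.

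**The case against.** The strongest reply is that the article does not describe visit-by-visit testing. A reader might infer from Table 1 that at least 17 tests will be run and that the preoperative scores will be ignored. The documents do not support either as a statement of fact. Table 1 is a collection schedule, and the test rules mention no instrument or visit. The same tests could be applied to a change score, a summary over time or the 6-month value alone, and the abstract points to 6 months for quality of life. This objection stands, so the count of 17 and its error rates are conditional. For the same reason, nothing can be concluded about patients with a missing questionnaire: no rule for them is stated.

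A second reply is that a condensed article may leave repeated-measures modelling and multiplicity to an analysis plan that is not shown. That is fair for what the article leaves silent. It does not cover the tests that it does name, because the Discussion, going through the CONSORT items, states that the statistical methods for the analysis are contained in the protocol. A better method than a stated one can be proposed.

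Third, the variance factors belong to linear adjustment against a comparison of means. They are not an exact measure of loss against a rank test, and the correlations are assumed. This also stands, which is why a range is shown.

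Fourth, pain and quality of life are secondary in a pilot that itself expects no significant secondary differences, and the primary outcome is binary and unaffected. This limits the importance of the point. It does not favour the unadjusted tests, since a pilot that feeds a larger trial gains from more precise estimates.

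**Conclusion.** The point holds in a limited form. The only methods named for continuous outcomes are unadjusted two-sample tests. They make no use of the preoperative VAS, EuroQol and SF-36 scores as covariates, or of the 6, 6 and 5 postoperative measurements as a series. Baseline adjustment would reduce variance by 9% to 49% for correlations between 0.3 and 0.7; the article gives no correlation, so that range is an assumption. The false-positive chance of about 26% to 58% applies only if every scheduled time is tested once per instrument, and depends on the correlation assumed; the 58% requires independence and should not be quoted alone. The mismatch between the two statistical sections needs no assumption, but it is minor. The change is worth making because it costs little; it does not threaten the trial's main conclusion.

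**What to change.** - Analyse each scale with a baseline-adjusted model: ANCOVA at the chosen time, or a mixed model for repeated measures over the postoperative times. Include the preoperative score and the stratification factors (center, earlier PD, earlier peritonitis).
- Prespecify one contrast per scale: week 26 for EuroQol and SF-36, matching the abstract, and one stated summary of early postoperative VAS pain, such as the mean from day 0 to week 2. That gives three main comparisons.
- Report estimates with 95% confidence intervals and treat the other times as descriptive.
- Reconcile Descriptive statistics and Univariate analysis by naming one test for the remaining continuous variables.
- Add a rank-based or transformed sensitivity analysis in case the scores are skewed.

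The cost is wording and modest extra analysis, with no new data or patients. The drawback is a linear-model assumption for bounded scores, which the sensitivity analysis addresses.

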#### Univariate analysis

Categorical variables will be compared with the Chi-square test. Continuous variables will be compared with the Mann-Whitney-U test or the two sample unpaired t-test.

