## Methods/Design

### Study objectives

Primary Objective: Does the use of the laparoscopic insertion technique lower the incidence of malfunctioning PD catheters at 6 weeks postoperatively?

Secondary Objectives: Does the use of the laparoscopic insertion technique improve catheter longevity and reduce the rate of surgical complications, mortality, leakage, catheter migration, re-admissions, exit-site infections, peritonitis and duration of hospital stay? Does the use of the laparoscopic insertion technique reduce postoperative pain, the use of postoperative pain medication and increase the quality of life? Does the use of the laparoscopic insertion technique lower the incidence of malfunctioning PD catheters at 6 months postoperatively?

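### Catheter longevity is a censored time, but no stated method handles censoring, and the logistic model for catheter survival has no time point

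*Protocol article*

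**What the plan says.** All references are to the protocol article.

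- **Objective (Study objectives).** The first secondary question is "Does the use of the laparoscopic insertion technique improve catheter longevity and reduce the rate of surgical complications". The same question is repeated under Study questions.
- **Outcome (Secondary outcomes).** The list reads "Catheter longevity, the rate of surgical complications, mortality, leakage, catheter migration, re-admissions, infections, and duration of hospital stay". No start, end event, horizon or censoring rule is given for longevity. The percentage of functioning catheters at 6 months is a separate outcome.
- **Summaries (Descriptive statistics).** "Continuous variables will be presented as medians (ranges"; categorical variables get counts and percentages.
- **Tests (Univariate analysis).** "Categorical variables will be compared with the Chi-square test", and "Continuous variables will be compared with the Mann-Whitney-U test or the two sample unpaired t-test".
- **Model (Multivariate analysis).** "Logistic regression will be applied to determine the independent effects of age, gender, ASA classification, body mass index, reason ESRD, time of surgery" and further factors, ending with "previous PD catheter insertion and previous abdominal surgery on catheter survival". No time point is attached to catheter survival.
- **Follow-up.** The last questionnaires are at week 26 (Table 1), function is last assessed at 6 months (Secondary outcomes), and records are verified at six months (Data collection and access to personal data).

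The statistical sections do not mention Kaplan-Meier, log-rank, Cox or any competing-risk method.

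**The concern.** Longevity is a time to failure, and for many patients the failure will not be seen. Most catheters should still be working at 6 months. Some patients may leave earlier with a working catheter: the Background names transplantation as another form of renal replacement therapy, and mortality is itself a secondary outcome.

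The only rule in the article that fits a duration is the one for continuous variables. Under it, a patient transplanted at week 8 with a working catheter enters the rank or t-test as 8 weeks, exactly like a catheter that failed at week 8. The chi-square test and logistic regression have the matching problem. A patient not followed to the time of interest must be called a failure, called a success, or dropped, and the article does not say which.

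At stake are the power and, if early leaving differs by arm, the validity of the longevity comparison. The Sample size calculation section says the pilot's outcome will be used to design a larger trial, so a distorted estimate could carry forward.

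**Working it through.** **No figure to reproduce.** The article sets 50 per arm without a power calculation, so the check is a simulation of what the stated methods would do.

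**Inputs**
- From the article: 50 per arm; two-sided 5% level; last assessment at 26 weeks; failure of up to 35% (open) and 13% (laparoscopic), from the Abstract.
- Assumed: the 35% and 13% are read as 26-week risks (the Abstract gives no horizon); constant hazards; early leaving with a working catheter is independent of failure, with a 26-week risk of 0% to 30%. The article gives no early-leaving rate.

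**Step 1. What the median would show.** Weekly hazard = −ln(1 − risk)/26.
- Open: −ln(0.65)/26 = 0.4308/26, so the true median is 0.6931 × 26/0.4308 = 41.8 weeks.
- Laparoscopic: −ln(0.87)/26 = 0.1393/26, so the true median is 0.6931 × 26/0.1393 = 129 weeks.
- With no early leaving, 65% and 87% of catheters are still working at 26 weeks, so the observed median is about 26 weeks in both arms. It falls clearly below 26 in the open arm only once 0.65 × (1 − c) < 0.50, that is, once early leaving c exceeds about 23%.

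The observed median therefore reports the follow-up limit. Kaplan-Meier would not reach a median either, so the useful summary is the failure probability at fixed times.

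**Step 2. Check of the simulation against a formula.** Two-proportion power at n = 50 for 35% v 13%, with pooled proportion 0.24:
- SE under the null = √(2 × 0.24 × 0.76/50) = 0.0854.
- SE under the alternative = √((0.35 × 0.65 + 0.13 × 0.87)/50) = 0.0825.
- Power = Φ((0.22 − 1.96 × 0.0854)/0.0825) = Φ(0.64) = 0.74.

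The simulated binary test with no early leaving gives 0.75, which agrees.

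**Step 3. Power with equal early leaving** (3,000 trials per row; simulation standard error at most √(0.25/3000) = 0.009). Mann-Whitney and t-test use observed time.

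| Early leaving, each arm | Log-rank | Mann-Whitney | t-test |
|---|---|---|---|
| 0% | 0.74 | 0.74 | 0.64 |
| 10% | 0.74 | 0.59 | 0.50 |
| 20% | 0.68 | 0.43 | 0.37 |
| 30% | 0.66 | 0.33 | 0.30 |

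With no early leaving, Mann-Whitney loses nothing: catheters working at 26 weeks are tied at the largest value.

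**Step 4. False-positive rate with no true difference (35% v 35%)**

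| Early leaving | Log-rank | Mann-Whitney | t-test | Binary, leavers = failure | Binary, leavers = success |
|---|---|---|---|---|---|
| 0% v 0% | 0.05 | 0.05 | 0.05 | 0.05 | 0.05 |
| 15% v 15% | 0.05 | 0.04 | 0.04 | 0.05 | 0.05 |
| 10% v 30% | 0.05 | 0.25 | 0.22 | 0.27 | 0.06 |

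**Step 5. Effect on a binary analysis.** With 20% leaving early in each arm, counting leavers as failures turns 35% and 13% into 1 − 0.65 × 0.80 = 48% and 1 − 0.87 × 0.80 = 30%. Counting them as successes gives about 31% and 12% (simulated).

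**The case against.** **The article does not say that leavers are failures.** A reader might infer that the plan counts transplantation, death or end of follow-up as catheter failure. No sentence says so, and the rule for continuous variables does not mention longevity. This stands: treating leavers as failures is a consequence of applying the listed methods literally, not a stated rule. It is also fair that a condensed article may leave censoring rules to an analysis plan. However, the article goes beyond silence: it gives one rule for all continuous variables and assigns a specific model to catheter survival.

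**Logistic regression may be right.** If catheter survival means functioning at 6 weeks or 6 months, both defined as binary outcomes, logistic regression is acceptable with complete follow-up. The defect is then only a missing time point. This stands as one reading, and the text does not settle it. It rules out a blanket replacement by Cox regression.

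**End of follow-up alone does no harm to the rank test.** It would be tempting to cite the high share of catheters still working at 6 months as proof that Mann-Whitney fails. Step 3 shows otherwise: 0.74 for both tests when nobody leaves early.

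**The sizes rest on assumptions.** The article gives no leaving rate and no horizon for the 35% and 13%, and nothing in it suggests that transplantation or death would differ between randomised arms. This stands. The false-positive result shows what could happen under unequal leaving, not what is expected.

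**The stakes are limited.** The primary outcome is binary at 6 weeks, and the Sample size calculation section expects no significant secondary differences. This stands and lowers the severity.

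**Conclusion.** The point holds in a limited form. A named secondary objective is a censored time, none of the stated methods handles censoring, and the model for catheter survival has no time point. Followed as written, the plan would report a median longevity that mainly reflects the 6-month limit.

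The loss to the tests depends on early leaving with a working catheter. For Mann-Whitney it is nil at 0%. At an assumed 10% to 30% in each arm, power falls to 0.59 to 0.33, against 0.74 to 0.66 for log-rank. At an assumed 10% v 30% with no true difference, the false-positive rate is about 0.25 against 0.05. These figures also assume constant hazards, independent leaving, and 35% v 13% as 6-month risks.

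Severity is minor to moderate. A reader might take this as a threat to the trial's main conclusion, but the choice of methods for censored times does not touch the binary 6-week primary comparison.

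**What to change.** 1. **Define longevity** as time from insertion to removal or revision for the failure reasons listed under Primary outcome.
2. **State the censoring rules.** Censor at end of follow-up and at transplantation with a working catheter. Say whether death with a working catheter is censored or treated as a competing event.
3. **Report** Kaplan-Meier (or cumulative-incidence) failure probabilities at 6 weeks and 6 months, in place of a median.
4. **Compare arms** with a log-rank test and a Cox hazard ratio with 95% CI. Stratify sparingly at most: the illustrative rates imply about 50 × 0.35 + 50 × 0.13 = 24 failures, while centre, past PD and previous peritonitis form at least 2 × 2 × 2 = 8 strata.
5. **Multivariate analysis.** Keep logistic regression only for binary catheter function at a named time point, and say how patients not followed to that point are handled. Use Cox regression if time to failure is meant.

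**Cost.** The change is mostly wording, with slightly more analysis. Dates of removal, revision, transplantation, death and last contact must be recorded. The article does not list the fields of the case record form, so this needs checking.
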